## Abstract

**Background:**

Heart failure with preserved ejection fraction (HFpEF) is a clinical syndrome characterized by diastolic dysfunction. Despite the increasing incidence of HFpEF, there is no available therapy that reduces the mortality rate of HFpEF. Zhigancao Tang has been used traditionally for the treatment of cardiovascular diseases in China. The use of traditional Chinese medicine (TCM) is associated with improvements in clinical syndromes and quality of life of patients. A randomized clinical trial should be conducted to provide clear evidence regarding the efficacy and safety of Zhigancao Tang granules for the treatment of HFpEF.

**Methods:**

A randomized, double-blinded, placebo-controlled clinical trial was proposed. A total of 122 patients with HFpEF will be randomly assigned to receive Zhigancao Tang granules or placebo for 12 weeks. The primary outcome measure is cardiac function. The secondary outcomes include measurement of the integral TCM syndrome score, echocardiography, 6-min walk test, N-terminal-pro hormone B-type natriuretic peptide level, atrial natriuretic peptide level, Minnesota Living with Heart Failure scale, and Lee’s scale. The outcome measures will be evaluated at baseline, 4 weeks, and 12 weeks. Adverse events will be evaluated from baseline till the 12-week follow-up period.

**Discussion:**

The results of this trial will demonstrate whether Zhigancao Tang granules are effective and safe for treating HFpEF.

**Trial registration:**

ClinicalTrials.gov NCT04317339. Registered on 23 March 2020.

**Supplementary Information:**

The online version contains supplementary material available at 10.1186/s13063-021-05232-6.

## Administrative information

The order of the items was modified to similar group items (see http://www.equator-network.org/reporting-guidelines/spirit-2013-statement-defining-standard-protocol-items-for-clinical-trials/).

## Background

### Introduction and rationale {6a}

Heart failure with preserved ejection fraction (HFpEF) is a clinical syndrome characterized by abnormal diastolic function caused by the impairment of left ventricular diastolic active relaxation and reduction of myocardial compliance. In recent years, the incidence of HFpEF has shown an increasing trend. Several studies have indicated that almost 50% of patients with heart failure have a preserved ejection fraction [1]. However, to date, there is no treatment option that can improve the outcomes in patients with HFpEF. This has led to difficulties in the management of chronic heart failure and public health, resulting in an increased economic burden.

The clinical manifestations of HFpEF are not specific, and its diagnosis is challenging. Typically, HFpEF is diagnosed based on symptoms such as fatigue, weakness, dyspnea, orthopnea, paroxysmal nocturnal dyspnea, and edema, as well as signs and evidence of preserved left ventricular ejection fraction (LVEF) and diastolic dysfunction [2].

In the general population, elderly women, rather than men, are at a higher risk of HFpEF [3]. Hypertension, atrial fibrillation, and obesity are commonly associated with HFpEF. Although the exact mechanism underlying HFpEF is yet to be clarified, several mechanisms have been proposed. These include structural remodeling (myocardial fibrosis and ventricular hypertrophy), inflammation, and microvascular dysfunction, leading to diastolic dysfunction owing to increased ventricular stiffness and decreased cardiac compliance [4].

In contrast to heart failure with reduced ejection fraction (HFrEF), there are a limited number of randomized controlled trials (RCTs) on patients with HFpEF. Furthermore, there is no treatment option available for HFpEF that can reduce the morbidity or mortality of patients. Current treatment strategies for HFpEF focus on symptomatic relief and screening of comorbidities. Diuretics are recommended to treat fluid overload, whereas other medications are not prescribed, as most hospitalizations and deaths are not attributed to chronic heart failure in patients with HFpEF. To improve the ability to exercise, the physical and diastolic function of patients with HFpEF and combined endurance and resistance training are recommended by the American College of Cardiology/American Heart Association and European Society Cardiology (ACC/AHA and ESC) [5].

Traditional Chinese medicine (TCM) involves multilevel and multitargeted treatment strategies with fewer side effects. Hence, it has been considered an alternative therapeutic strategy for treating heart failure [6, 7]. According to TCM theory, qi and yin deficiency are the primary syndromes in the early stage of heart failure. Zhigancao Tang is recorded in the Treatise on Exogenous Febrile Disease and has been used for the treatment of arrhythmia associated with qi and yin deficiency and various types of asthenia [8, 9]. Qi and yin deficiency are common syndromes in TCM, characterized by fatigue, shortness of breath, spontaneous perspiration or night sweating palpitation, dry mouth, and rapid pulse, which are often observed in cases of cardiovascular diseases as well [10]. Zhigancao Tang is composed of *Radix Rehmanniae Recens*, *Ramulus Cinnamomi*, *Radix Glycyrrhizae*, *Rhizoma Zingiberis Recens*, *Radix Glehniae*, *Radix Ophiopogonis*, *Fructus Cannabis*, and *Fructus Jujubae* (Table 1). In our previous trial, we confirmed that Zhigancao Tang can restore cardiac function and improve the quality of life in patients with heart failure. We intend to conduct a randomized, double-blind, placebo-controlled trial to further evaluate the efficacy and safety of Zhigancao Tang in the treatment of qi and yin deficiency-associated HFpEF. Based on the clinical findings from this study, a novel treatment option for HFpEF can be proposed.

**Table 1 Tab1:** Components of Zhigancao Tang granules

Chinese name	Latin name	English name	Plant part
Zhigancao	*Radix Glycyrrhizae*	Honey-fried licorice root	Root
Shengjiang	*Rhizoma Zingiberis Recens*	Ginger	Root
Guizhi	*Ramulus Cinnamomi*	Cassia twig	Twigs
Beishashen	*Radix Glehniae*	Coastal glehnia root	Root
Shengdi	*Radix Rehmanniae Recens*	Dried rehmannia root	Root
Maimendong	*Radix Ophiopogonis*	Ophiopogon	Root
Maren	*Fructus Cannabis*	Edestan	Seeds
Dazao	*Fructus Jujubae*	Jujube	Fruits

### Objectives {7}

The aim of this RCT  is to evaluate the efficacy and safety of Zhigancao Tang granules for the treatment of HFpEF. The study hypothesizes that cardiac function can be improved significantly with Zhigancao Tang granule treatment, compared to that achieved using placebo treatment.

### Trial design {8}

This is a randomized, double-blind, placebo-controlled clinical trial. The aim of this study is to assess the safety and effectiveness of Zhigancao Tang granules in treating qi and yin deficiency-associated HFpEF.

## Methods: participants, interventions, and outcomes

### Study setting {9}

The study will be conducted at the Longhua Hospital affiliated to Shanghai University of Traditional Chinese Medicine (Xuhui District, Shanghai), a traditional Chinese medicine hospital that combines medical, teaching, and research domains. A total of 122 participants will be recruited from Longhua Hospital affiliated to the Shanghai University of Traditional Chinese Medicine and randomized into Zhigancao Tang and placebo groups. The trial was registered at ClinicalTrials.gov (NCT04317339).

#### Recruitment

Participants will be recruited from the Longhua Hospital affiliated to Shanghai University of Traditional Chinese Medicine. The patients will be informed about the objectives, approaches, potential adverse effects, and advantages of this trial. The planned enrollment period is 25 weeks.

#### Participant screening

All patients diagnosed with HFpEF will undergo laboratory blood testing before enrolment. The testing will include routine blood, urine, and liver and kidney function analyses. Electrocardiography will also be performed.

### Eligibility criteria {10}

#### Inclusion criteria

Compliance with the diagnostic criteria of Western medicine for HFpEF [2] and diagnostic criteria for TCM syndromes of qi-yin deficiencyCardiac function classification by New York Heart Association (NYHA; grades I to III)Age between 30 and 80 yearsThose who volunteered to participate in clinical trial observation and signed the informed consent formNo intake of concomitant drugs during the observation period, except for those specifiedCompliance with treatment completion and follow-up

#### Exclusion criteria

History of valvular heart disease, restrictive cardiomyopathy, or pericardial diseaseUnstable decompensated heart failure after treatmentPresence of atrial fibrillationPatients with severe lung, liver, endocrine system, and kidney dysfunctionPatients with cancer and other common malignant diseases that can reduce life expectancyPregnant or lactating womenAllergic constitution or history of allergy to common drugsPatients with mental illness or poor compliance with TCM treatment

### Who will take informed consent? {26a}

The researchers will design the questions, recruit patients, and conduct the study. Patients will receive written information about the trial and decide if they would like to sign the informed consent form and participate in the study.

### Additional consent provisions for collection and use of participant data and biological specimens {26b}

We will confirm with the participants if their data may be used and request them to share data with the other relevant authorities.

## Interventions

### Explanation for the choice of comparators {6b}

The Zhigancao Tang granule placebo was selected as the comparator to demonstrate the efficacy and safety of Zhigancao Tang granules and decrease bias.

### Intervention description {11a}

#### Zhigancao Tang granule intervention

In the Zhigancao Tang group, patients will be orally administered a solution of the Zhigancao Tang granules in 50 mL of hot water twice a day for 12 weeks. The Zhigancao Tang granules were prepared from *Radix Rehmanniae Recens* (Shengdi, 15 g), *Ramulus Cinnamomi* (Guizhi), *Radix Glycyrrhizae* (Zhigancao, 12 g), *Rhizoma Zingiberis Recens* (Shengjiang, 9 g), *Radix Glehniae* (*Beishashen*, 30 g), *Radix ophiopogonis* (*Maimendong*, 12 g), *Fructus Cannabi*s (*Maren*, 9 g), and *Fructus Jujubae* (Dazao, 10 g).

#### Zhigancao Tang granule placebo

The placebo used will contain 10% Zhigancao Tang. Patients in the control group will consume the placebo at the same dose and schedule as those followed by patients in the Zhigancao Tang group. Both Zhigancao Tang granules and placebo will be supplied by the Chinese medicine pharmacy of Longhua Hospital affiliated to the Shanghai University of Traditional Chinese Medicine, with similar labels and packaging.

#### Basic treatment

If necessary, basic treatment could be administered as follows [2]:
Treatment of volume overload: sodium intake should be restricted to 2 g/day. Thiazide-like diuretics, loop diuretics, and aldosterone receptor antagonists should be administered based on the symptoms and body weight of the patients.Treatment of coexisting conditions: patients with hypertension or kidney disease should receive angiotensin-converting enzyme inhibitors (ACEIs), angiotensin receptor blockers (ARBs), angiotensin receptor neprilysin inhibitors (ARNIs), and medical therapies. Revascularization should be considered in patients with coronary artery disease and clinical angina.

### Criteria for discontinuing or modifying allocated interventions {11b}

The criteria for discontinuation are as follows: (1) if anaphylaxis or serious adverse events occur, the test should be terminated based on the physician’s decision; (2) during the study, two consecutive laboratory tests will be compared, and the results of laboratory tests should be factored in while judging treatment efficacy and safety; (3) patients with poor compliance in the study (compliance with experimental drug < 80%), those with automatic halfway dressing change, or those administered other Chinese and Western drugs prohibited by the party; (4) cases of blinding not maintained halfway through the study for various reasons; (5) regardless of reason, unwillingness or inability of the patient to continue with the clinical study, or request of withdrawal from the study to the competent physician; (6) loss of patients owing to non-acceptance of the drug or the test, even when the study case did not explicitly propose withdrawal from the study.

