**Fig. 1 Fig1:**
[figure not shown]
Flow diagram of the study process

**Table 4 Tab4:** Schedule of enrollment and assessments

Study period					
Time point	Enrolment	Allocation	Post-allocation		Follow-up
	−1 week	Week 0	Week 4	Week 12	Week 24
Enrolment					
Eligibility screen	×				
Informed consent	×				
Allocation		×			
Interventions					
Zhigancao Tang granules					
Zhigancao Tang granule placebo					
Outcome assessments					
Cardiac function		×	×	×	×
Echocardiography		×	×	×	×
Lee’s scale		×	×	×	×
MLHFQ		×	×	×	×
6MWT		×	×	×	×
NT-pro BNP, ANP		×	×	×	
ITSS		×	×	×	×
Safety assessments					
Blood routine		×		×	
Urine routine		×		×	
Liver and kidney function		×		×	
electrocardiograph		×		×	
AE		×	×	×	×
Compliance assessments			×	×	

AE, adverse events; ANP, atrial natriuretic peptide; ITSS, integral Chinese medicine syndrome score; MLHFQ, Minnesota Living with Heart Failure questionnaire scale; NT-proBNP, N-terminal pro-brain natriuretic peptides

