## Data collection and management

### Plans for assessment and collection of outcomes {18a}

In this 24-week trial, all participants will be treated with the Zhigancao Tang granules or placebo for 12 weeks, with follow-up continuing for another 12 weeks. Data will be recorded in the case report forms (CRFs) at each visit and entered in Microsoft Excel by two statisticians working independently.

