#### Missing data

Any missing data will be treated as a failure using the intention-to-treat principle, and the reason will be recorded.

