### Methods in analysis to handle protocol non-adherence and any statistical methods to handle missing data {20c}

We will perform per-protocol and intention-to-treat analyses. Participants with poor compliance (compliance of experimental drug < 80%) or those no longer receiving medication and undergoing testing during the study will be excluded from the per-protocol analysis. Researchers will be advised to take active measures to complete the last test if the participants drop out of the trial or are lost to follow-up for the intention-to-treat analysis. Missing data will be imputed using a multiple imputation procedure via chained equations.

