### Adverse event reporting and harms {22}

Adverse events will be recorded and reported to the researchers, including the timing, severity and duration, actions taken, and outcomes. Zhigancao Tang granules may cause diarrhea, abdominal distension, dizziness, and anaphylaxis. The researchers will record the adverse events and decide whether to terminate the treatment based on the patient’s condition and report the same to the DMC and ethics committee. Other unintended effects of trial interventions or trial conduct will also be reported.

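### Study-drug compliance below 80% is by itself a reason to discontinue a randomised patient, and visits to week 24 are not secured for those stopped

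*Protocol article*

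**What the plan says.** Section 11b of the protocol article lists the criteria for discontinuation. Item (3) includes "patients with poor compliance in the study (compliance with experimental drug < 80"%). Physician judgement is written only into item (1), on anaphylaxis and serious adverse events. Item (5) concerns "unwillingness or inability of the patient to continue with the clinical study" and item (6) concerns loss of the patient, so one list covers both stopping the drug and leaving the study.

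Other sections bear on the same patients:

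- **Table 4** has a row "Compliance assessments" marked at weeks 4 and 12. Cardiac function, the primary outcome, is scheduled at baseline and at weeks 4, 12 and 24.
- **Section 18a** plans 12 weeks of treatment "with follow-up continuing for another 12 weeks".
- **Section 20c** promises both intention-to-treat and per-protocol analyses and leaves out of the latter "Participants with poor compliance (compliance of experimental drug < 80"%). For leavers it says: "Researchers will be advised to take active measures to complete the last test if the participants drop out of the trial". It also prescribes multiple imputation.
- **The Missing data paragraph** says: "Any missing data will be treated as a failure using the intention-to-treat principle".

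**The concern.** Low adherence is something that happens after randomisation. An intention-to-treat comparison should include it, and a per-protocol analysis may set it aside. Here it becomes an instruction to discontinue. Followed as written at week 4, the rule turns partial exposure into none. That shrinks the treatment contrast even when every outcome is still measured.

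The second risk is loss of outcomes. The list does not separate stopping drug from leaving the trial, and no sentence keeps a patient stopped under item (3) on the visit schedule. If outcomes then go missing and are scored as failures, response rates fall in both arms and power drops further.

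If low compliance is more common in one arm, the comparison is also biased. Section 22 states that "Zhigancao Tang granules may cause diarrhea, abdominal distension, dizziness, and anaphylaxis", so gastrointestinal effects could lower compliance on active treatment. The protocol gives no compliance rates by arm, so this is a possibility only.

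**Working it through.** **1. What the text secures.** Section 11b gives the rule without a time point. Table 4 allows it to act at week 4 or week 12.

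- Acting at week 4: 12 − 4 = 8 of the 12 treatment weeks are lost, and the week-12 and week-24 visits are at risk.
- Acting at week 12: no exposure is lost, and the week-24 visit is at risk.

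The only provision aimed at leavers, in section 20c, is advisory. It covers one unspecified last test, and it speaks of patients who drop out or are lost rather than those whom the investigator takes off drug. Section 18b offers reminders and fare reimbursement to everyone. Follow-up is therefore not prevented, but it is not secured.

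**2. The plan's own sample size.** Inputs from section 14: 93.3% versus 73.3%, alpha 0.05, power 80%. The two-sided test is from section 20a. With unpooled variance:

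n = (1.960 + 0.842)² × (0.933 × 0.067 + 0.733 × 0.267) / 0.200² = 50.7, so 51 per group, as stated. Then 51 × 1.2 = 61.2, written as 61.

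**3. Power formula.** Normal approximation with pooled variance under the null, n per group:

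power = Φ[(d − 1.96 × SE0) / SE1], with SE0 = √(2p̄(1 − p̄)/n) and SE1 = √((p1(1 − p1) + p2(1 − p2))/n).

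No discontinuation, n = 61: d = 0.200, p̄ = 0.833, SE0 = 0.0675, SE1 = 0.0651. This gives Φ(1.04) = 85.1%.

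**4. Effect of the rule.** Let s be the share discontinued in each arm. It is assumed, because the protocol does not give it. No other losses are assumed.

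- **A.** All outcomes collected; active patients off drug respond at the control rate. Active (1 − s) × 0.933 + s × 0.733; control 0.733.
- **B.** As A, but half of those discontinued have missing outcomes scored as failures. Active (1 − s) × 0.933 + (s/2) × 0.733; control 0.733 × (1 − s/2).
- **C.** All those discontinued have missing outcomes scored as failures. Active 0.933 × (1 − s); control 0.733 × (1 − s).

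| s per arm | A | B | C |
|---|---|---|---|
| 5% | 80% | 77% | 74% |
| 10% | 75% | 68% | 63% |
| 20% | 62% | 52% | 47% |

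At s = 10% the rates are 91.3% vs 73.3% (A), 87.6% vs 69.6% (B) and 84.0% vs 66.0% (C). For A: d = 0.180, p̄ = 0.823, SE0 = 0.0691, SE1 = 0.0672, so Φ(0.66) = 74.6%. The difference is 18 points in all three cases. Power falls from A to C because both rates move towards 50% and the variance rises. If the 10% are simply left out (55 per group), power is about 81%.

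**5. Unequal shares, scored as failures.** With 20% discontinued on active and 10% on control: 0.933 × 0.8 − 0.733 × 0.9 = 0.746 − 0.660 = 8.7 points, power about 18%. Reversed: 0.933 × 0.9 − 0.733 × 0.8 = 0.840 − 0.586 = 25.3 points, power about 88%. The bias can run either way; an excess in the active arm works against the granules.

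**The case against.** The strongest reply is that the harm depends on readings the text does not force. Compliance may be meant as an overall figure judged at the end of treatment, in which case no exposure is lost. Even a week-4 stop need not lose the week-4 cardiac function assessment, which falls at the same visit. Section 11b does not say that such patients leave the study, sections 18a and 18b apply to all participants, and a condensed article may leave visit rules for patients off drug to the full protocol.

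The figures can be challenged too. B and C are driven mainly by failure scoring, which conflicts with the multiple imputation of section 20c and is a separate matter. A assumes that low compliers left on drug would have kept the full 93.3% response. If they kept half the benefit, active response at 10% would be 0.9 × 0.933 + 0.1 × 0.833 = 92.3% and power 80.2%, so the rule itself costs about 5.5 points (80.2% to 74.6%). At 5% it costs about 2.5 points (82.7% to 80.2%). The plan aims at 80%, and A at 5% still meets that.

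All of this limits the size, and it stands to that extent. It does not remove the defect. The 80% rule is stated outright under a heading on discontinuing allocated interventions, so it is not detail left elsewhere. An investigator following it could stop treatment at week 4. If the intent was only a per-protocol label, the sentence says something else and needs correcting. The 20% loss allowance does not rescue the failure-scored cases, because it covers patients who are not evaluable, not patients counted as failures.

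**Conclusion.** The concern holds. Section 11b makes compliance below 80% a stand-alone, non-safety reason to discontinue, and the protocol does not secure visits to week 24 for patients stopped on that ground. The per-protocol definition in section 20c already does what the cutoff is needed for.

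The size is uncertain, since neither the share below 80% nor the visit at which the rule acts is given. With 5% to 20% per arm, and against 85% with no discontinuation, power would be 80% to 62% if all outcomes are kept and 74% to 47% if all are missing and scored as failures. The first range gives an upper bound on the loss from stopping drug alone. The further loss in the second comes from failure scoring and would be smaller with last tests obtained or with multiple imputation. Bias from unequal compliance is possible but has no figures in the protocol to support it. The change is worth making because it is cheap, not because a large loss has been shown.

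**What to change.** In section 11b, delete compliance below 80% from item (3), or state there that low compliance alone ends neither treatment nor participation. Add that any patient taken off study drug, for whatever reason, keeps all scheduled visits to week 24 unless consent is withdrawn. Keep the 80% cutoff in section 20c, where it defines the per-protocol set.

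The cost is a change of wording in one section, with no extra patients and no visits beyond those in Table 4. The small downside is that some patients with low exposure stay in the intention-to-treat set, which the planned per-protocol analysis addresses.

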### Strategies to improve adherence to interventions {11c}

The drug quantity and date of drug intake by each patient will be recorded. The patients will be required to return any unused drugs during each visit, which will be recorded by the researchers.

